### Sample size

Twenty-two ICUs will be included, each with a total of 150 patients in each branch of the study until completing a sample size of 3.300 patients. The calculation for this sample considered the rate of pressure ulcers observed in PENFUP phase 1 (7.5%) in the control group (patients who received preventative care with skin moisturizing) [17]. As a result of this process, it was decided that the highest incidence rate acceptable for the conventional group for repositioning would be 0.075 and that the incidence in the intervention group with high repositioning frequency would be 0.023 (2.3/7 = 0.32).

For the hypothesis of the study, we calculated a 50% low-impact reduction in pressure ulcers in ICUs that execute repositioning at a high frequency (intervention group A), compared to the ones that implement repositioning at conventional care or control group. The number of ICUs and individuals in there would be obtained by a calculation considering an intra-class correlation coefficient of 0.035 previously attained in the Chaboyer study et al. (2016), a power of 80%, and an alpha error of 0.05% resulting in a 50% difference between both intervention groups [18].

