#### Control group B (conventional care)

The units randomized to this care will be labeled as conventional care will not implement any intervention. Patients in this group will receive the usual care for repositioning applied at any frequency.

Furthermore, patients from both groups will receive all other interventions that are currently applied in their hospitals regarding the prevention of PUs according to their hospital’s protocols. Additionally, repositioning will be performed according to routine practices related to initiation, interruption, re-initiation, or finalization of posture changes, depending on the state of health of each patient, medical orders, and nursing decisions. Patients recruited in each ICU will be follow up when they develop their first PU (stage I), or when they begin the autonomous mobilization [ambulation], or when they are transferred to service to another hospital, or they discharge to their homes, or if they die in the ICU.

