### Classification of pressure ulcers

Pressure Ulcers would be classified as grade I to IV according to The Pressure Ulcer Advisory Panel Consensus Development Conference [21] (NPUAP) 1989, and the National group for the study and counseling in Pressure Ulcers and Chronic Wound-Spain [22] (GNEAUP), 2003. We did not use the new pressure ulcer terminology (pressure injury) and the updated stages provided by The National Pressure Ulcer Advisory Panel- NPUAP, given that all hospitals in our country follow the Ministry of Health Guidelines according to the primary pressure ulcers classification and also Pus are reported in this way.

This system, accepted until very recently, establishes four stages for pressure ulcers. The main objective of any classification system is to standardize the collection of information and provide a standard description of the severity of the ulcer for both clinical practice, evaluation, or research purposes.

This classification defines ulcers from grade I to grade IV. Grade I describes an ulcer with erythema that does not pale on intact skin. Edema, induration, discoloration, and local heat are seen in dark-skinned patients. Stage II is described as a partial skin loss that affects the epidermis, dermis, or both. It is classified as a superficial ulcer with the appearance of abrasion, blister, or shallow crater. Grade III ulcer is described as a total loss of skin thickness that involves injury or necrosis of the subcutaneous tissue, which may extend downward but not through the underlying fascia. Stage IV is considered the total loss of thickness with extensive destruction, tissue necrosis, or injury to muscle, bone, or supporting structure. In this stage, lesions such as caverns, tunnels, or winding paths can occur. This classification is the currently way each hospital has to report PU to the Ministry of Health and Social Protection in Colombia.

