Each center will designate a leader responsible for the PENFUP phase 2 study procedures in each ICU. Each leader must ensure the complete execution of the project day by day and the accurate application of the assigned intervention in each shift. The healthcare staff assigned to group A (high frequency each 2/ h) will receive automatic text messages by cellphone twice a week to remind the intervention frequency to be applied. Leaders from each center will designate two groups of data collectors to operate based on the informed consent given by patients or their families and will gather information of each intervention day bay day in a register format to be completely archived into the study’s platform, including the number of total daily posture shifts per patient in each ICU.

Each center will receive a set of general initiation instructions in person or via teleconference or internet conference. Each center will also receive the investigators’ manual and questionnaires for collecting data to be included in the study’s platform. The total of postural shifts in 24 h will be registered to maintain proper management of the number of shifts per patient calculated for both high and conventional care. Other variables that will be included contain information of each hospital (the type of hospital, total number of nurses, relation nurse-patients, type of prevention protocols for pressure ulcers, and incidence of a pressure ulcer from the year before the beginning of the study); and patient variables (demographic, health history, health status in ICU, complications in ICU, pressure ulcers and location, repositioning complications and reason of ICU discharge) (Table 1).

**Table 1 Tab1:** Variables and timeline for inclusion by each ICU. The complete timeline for each ICU is about 3–4 months

Variables and time to collection 1–4 Months by ICU	Variable to be obtained in each ICU				Type of variable by ICU by Intervention and Control			
**Months 1 to 4**	**T1√**	**T2√**	**T3√**	**T4√**	**T1√**	**T2√**	**T3√**	**T4√**
**1-Primary Outcome**	Development of new pressure ulcers in clusters: ▪ Areas defined of injury: sacrum, heels, ankles, elbows, hip, scapula ▪ Others				Rate ulcers per ICU /total control Rate ulcers per ICU/total intervention Median (IQR).			
	Stage of ulcers: I, II, III, IV + o Indeterminate				Total ulcers per stage per ICU per group /150 patients N (%) by cluster			

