### Statistical analysis

All ICUs shall be analyzed according to the branch they were randomized to (Intention to treat) [7, 23]. The incidence of PU will be analyzed considering the time of natural first appearance; that is, within the time-lapse in which the patients are in the study. The two-time variables to be considered for this analysis will be admission into the ICU and the emergence of PUs since the time of admission for each patient. Also, we will include the length of stay in the ICU. The characteristics of the clusters and each individual will be analyzed considering counts (%), means (SD), medians (interquartile range). The percentage of applied interventions (repositioning) by clusters in each group will be computed according to the total of interventions that should be administered in both branches of high frequency and conventional care. The primary analysis will be done at the cluster level (ICU) and the secondary at an individual level (each patient). When analyzing at a cluster level, the total number of PUs will be divided by the total of accumulated days of each patient in each cluster to obtain incidence rates in both groups; this is done based on the permanence of the patients from each cluster. To calculate the incidence rate (IR of 95%), the incidence rate in the groups with a higher frequency of postural changes in group A will be divided by the control groups’ incidence rate of postural changes in group B. The incidence of PU will be analyzed considering the time of natural first appearance; that is, within the time-lapse in which the patients are in the study.

The secondary result includes evaluating the frequency of the severity of PUs (stages I - IV) and will be compared with both groups using an adjusted Chi-square test. For the individual evaluation of the risk of PUs in patients, the first PU to appear in each patient will be considered for calculating the rate of events and time before the event. The hazard ratio (HR) will be computed using Cox proportional-hazard models and its corresponding 95% confidence intervals (CI), adjusted by the standard error by cluster (SE) [23]. The Cox models will be implemented for exploring relations between the main result and the explanatory considering the time before the time of occurrence.

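### Ulcer severity is compared with a chi-square test that ignores stage order, gives no estimate and, if run among ulcer-bearing patients, can point the wrong way

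*Protocol article*

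**What the plan says.** The protocol article names one method for severity, under Statistical analysis: "evaluating the frequency of the severity of PUs (stages I - IV) and will be compared with both groups using an adjusted Chi-square test". It does not say what the test is adjusted for, and it gives no effect measure for severity. In the same section, time to first ulcer receives a hazard ratio with a 95% confidence interval and a standard error adjusted for cluster.

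Classification of pressure ulcers sets out an ordered scale: "This classification defines ulcers from grade I to grade IV", from erythema on intact skin up to destruction reaching muscle or bone. It says the purpose of such a system is to "provide a standard description of the severity of the ulcer for both clinical practice, evaluation, or research purposes".

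Table 1 (Data collection and procedure) describes the stage output as "Total ulcers per stage per ICU per group /150 patients N (%) by cluster", and lists the categories as "Stage of ulcers: I, II, III, IV + o Indeterminate". So the table divides by patients, while the analysis sentence speaks of the severity of the ulcers. The article does not say which denominator the test uses.

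**The concern.** There are two separate problems.

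First, the test does not fit the scale. A chi-square on four stages in two arms spends 3 degrees of freedom on any difference in pattern and gives only a p-value. It cannot say which arm has the worse ulcers or by how much. If the adjustment is for clustering, it corrects the variance and does not restore the order.

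Second, the denominator matters more than the test. If the table holds only patients who developed an ulcer, the arms are compared in a group formed after randomization by the event that repositioning is meant to prevent. An intervention that prevents mild ulcers and leaves the others alone would then show a more severe stage mix. A reader could take a benefit for harm. This also sits badly with the section's commitment to analyse units as randomized.

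**Working it through.** **Inputs.** From Sample size and Randomization: 22 ICUs of 150 patients, 1:1, so 11 × 150 = 1,650 per arm; control incidence 7.5%; intervention incidence 3.75% (the 50% reduction) or 2.3% (also stated); intra-class correlation 0.035. The stage mix and the size of any severity effect are not in the document and are assumed below.

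**The plan's own figure.** The article gives no power for severity, only the total of 3,300.
- Two-proportion formula at 7.5% vs 2.3%, two-sided 5%, 80% power: n = [1.96·√(2·0.049·0.951) + 0.842·√(0.0694 + 0.0225)]² / 0.052² ≈ 270 per arm.
- Design effect: 1 + 149 × 0.035 = 6.215. Then 270 × 6.215 ≈ 1,678 per arm, about 3,356 in total, close to 3,300.
- With a 50% reduction the same steps give 592 × 6.215 ≈ 3,679 per arm.
- Effective patients per arm: 1,650 / 6.215 ≈ 265.

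**Step 1: reversal among ulcer-bearing patients.** This is an illustration that uses the 50% reduction in total incidence.

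| | Control | Frequent repositioning |
|---|---|---|
| Stage I, of all patients | 4.5% | 0.75% |
| Stage II or worse, of all patients | 3.0% | 3.0% |
| Any ulcer | 7.5% | 3.75% |
| Stage II or worse, of ulcers | 3.0/7.5 = 40% | 3.0/3.75 = 80% |

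Per patient, the ratio for stage II or worse is 3.0/3.0 = 1. Among ulcers it is 80/40 = 2. No patient is worse off.

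**Step 2: cost of ignoring order, stages I to IV among ulcers.** For a pure trend, a 3-df and a 1-df test share the same noncentrality, so the loss is bounded whatever the stage mix. The largest gap is 66.2% − 49.2% = 17.0 points. Examples use 1,650 × 0.075 ≈ 124 control ulcers and 1,650 × 0.0375 ≈ 62 or 1,650 × 0.023 ≈ 38 intervention ulcers, with no discount for clustering:
- Mix 50/35/10/5%, odds ratio 0.5: chi-square 42.9% vs ordered test 59.5% (62 ulcers); 30.7% vs 44.9% (38 ulcers).
- Mix 90/8/1.5/0.5%, odds ratio 0.5: 13.0% vs 19.5%; 10.2% vs 14.6%.
- Odds ratio 0.8, any mix tried: a gap of about 1 to 4 points.
- Not a trend, 50/35/10/5% against 60/20/10/10%: chi-square 47.3%, ordered test 10.4%.

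**Step 3: all patients, five categories (none, I to IV), common odds ratio, 265 effective patients per arm.**

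| Incidence | 4-df chi-square | Rank (ridit) test | Any ulcer vs none |
|---|---|---|---|
| 7.5% vs 3.75% | 28.3% | 46.7% | 46.6% |
| 7.5% vs 2.3% | 58.6% | 79.3% | 79.3% |

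The rank test matches the plain incidence comparison because at least 92.5% of patients have no ulcer. In this same model, restricted to ulcers, the chi-square and the ordered test both have about 5% power: a control mix of 60/30/8/2% becomes about 61/29/8/2%, so there is almost no severity shift to find.

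**Step 4: the step 1 example, all patients.** The 4-df chi-square has 56% power and the rank test 44%. A single ordinal summary is therefore no remedy by itself. It would also report a benefit across the scale when stage II or worse has not changed.

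**The case against.** A reader might infer that the chosen test throws away about 20 points of power. The documents do not support that. They give no stage mix and no severity effect. A gap of 18 to 21 points appears only when patients without an ulcer form a fifth category and the odds ratio is common across stages, and step 3 shows that this gain is the incidence comparison over again. For the four stages named in the sentence, 17 points is the ceiling for a pure trend, and the chi-square can win otherwise.

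A reader might also infer that the plan definitely restricts the test to ulcer-bearing patients. It does not say so. That is the more natural reading of the analysis sentence, but Table 1 divides by 150 patients. The reversal is conditional on that reading, and the point is that the text leaves it open.

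Three further arguments deserve weight:
- The planned counts per stage and group would show direction descriptively. True, but without an estimate or an interval, and the named test would still supply the formal conclusion.
- The full protocol may define the adjustment. True, so its absence from the article is not held against the plan. The choice of a chi-square for this outcome is stated in the article.
- The stakes are low. Severity does not appear under Outcomes, and follow-up has this end point: "Patients recruited in each ICU will be follow up when they develop their first PU (stage I"). If most ulcers are recorded at stage I, any analysis of stage will carry limited information. This stands, and it caps the importance of the point.

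**Conclusion.** The point holds for the form of the analysis. An ordered scale is given an unordered test with no estimate, and the denominator is unsettled between the analysis sentence and Table 1. On the ulcer-bearing reading, a benefit confined to stage I would double the apparent share of ulcers at stage II or worse (40% to 80%) with nobody worse. That figure is an illustration of the mechanism, not a forecast. It assumes that 4.5 of the 7.5 percentage points in control are stage I.

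No definite loss of power can be claimed. Under trends of assumed size among ulcers, the examples run from about 1 to 17 points, and the sign reverses for patterns that are not a trend. The primary analysis is untouched. This is a change worth making to a secondary result.

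**What to change.** Replace the chi-square sentence with an analysis of all patients as randomized, using the same denominator as Table 1. Count each patient once and report three cumulative outcomes by arm: any ulcer, stage II or worse, and stage III or worse. Give each a cluster-adjusted ratio with a 95% confidence interval. Keep the stage table as description, and do not test the stage mix among ulcer-bearing patients.

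A cluster-adjusted common odds ratio over none and I to IV may be added. It should not replace the stage II or worse estimate, because with over 90% of patients ulcer-free it largely repeats the incidence result.

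State a rule for ulcers of indeterminate stage, for example counting them as an ulcer and placing them once at the lowest and once at the highest stage in a sensitivity analysis.

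The cost is a few sentences and no new data, since stage is already recorded. The price is candour about precision. At 3.0% in both arms and 265 effective patients per arm, the standard error of the log ratio is √(2 × 0.97 / (265 × 0.03)) ≈ 0.49, so a ratio of 1 would have an interval of about 0.38 to 2.6. This assumes that the planned intra-class correlation also applies to the higher stages. Stage III or worse will be less precise still and should be read as descriptive.

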## Background

Pressure ulcers (PU) are wounds that affect the skin, caused by prolonged contact or friction in certain points where increased mechanical pressure is applied by the patients’ own weight, especially under skeletal prominence areas (such as the sacrum, trochanters, scapulae, or shoulder blades, heels, and elbows) [1–3]. An increased rate of these events and their complications determine changes in the physical and mental state of the patients and their families, a decreased quality of life level, in addition to higher hospital costs and an increase in healthcare system expenses [1].

The absence of pressure ulcers is considered a quality indicator for installed safety programs and special care given to patients at hospitalization-level risk; therefore, prevention plans for these events should be implemented in patients at a higher risk. Even though considered preventable, PUs constitute between 10 and 50% of adverse events while affecting between 30 and 50% of patients at high and very high risk, especially those hospitalized in critical care services [2, 4]. The incidence of PUs in patients admitted into ICUs varies from 3,3 and 52,9% worldwide [5]. .These patients suffer a diminishing of their natural perception due to the effects of sedation and analgesia required for these services. As a result, a chronic and painful pressure over any area of the body produces little to no reaction in patients for them to change their position.

Among the different factors associated with the emergence of PUs, there is age (OR 2.14 [95% IC 1.27–3.62]), diabetes (OR 5.58 [95% IC 1.58–18.7), duration of MBP < 60-70 mmHg (OR 1.09 [95% IC 1.02–1.17]), mechanical ventilation (OR 23 [95% IC 6.42–86.6]), continuous venovenous hemofiltration or intermittent dialysis (OR 3.7 [IC 95% 1.03–13.86]), use of vasoactive drugs (OR 1.02[95% IC 1.02–1.03]), use of sedatives (OR 1.02 [95% IC 1.01–1.03]) and a low amount of shifts in position (OR 3.63 [95% IC 1.09–12.05]). The information proved that wounds due to pressure and pressure ulcers occur more frequently in patients who are hardly mobilized at lower rates in 24 h (OR 3.63 IC 95% [1.09–12.0]), meaning a repositioning rate of 4 times in 24 h [5, 6]; and a likelihood of 2,96 for grade II pressure ulcers (95% IC 1.23–7.15) [6].

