### Inclusion and exclusion criteria

Criteria for clusters (ICUs) inclusion: ICUs that admit adult patients (≥ 18 years) in critical condition, with any type of care emphasis (surgical, medical, neurological, or a mixture of any), with a minimum of 10 beds, that submit the feasibility survey and agree to commit to the care assigned in the randomization until including the total number of the sample. At least one ICU will be included from each hospital. In case one hospital may participate with more than one ICU, the units should have to receive the same allocation resulting from the randomization.

Criteria for clusters exclusion: intermediate care units or coronary care units in which patients are self-mobilized; or critical units for burned patients. Also, units destined for the care of patients with Covid 19 in which the standard of repositioning is between every 12–16 h.

Criteria for patient inclusion in each cluster: all patients are eligible as long as they are completely unable to move, have their skin intact at the moment of their admission into the ICU, are care-dependent for their complete mobilization (including unconsciousness, being under sedation or assisted ventilation), and are scheduled for a hospitalization period of at least 48 h.

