**1–4 Months by ICU**	**T1√**	**T2√**	**T3√**	**T4√**	**T1√**	**T2√**	**T3√**	**T4√**
**2-Secondary Outcome**	Complications during repositioning				Categorical: Hemodynamic changes, Respiratory Changes, ventilator changes, others.			
	Risk of PU in individuals				Hazard ratio (HR) Date of appearance of the PU (day-month-year) Time to the event (survival analysis)			
**1–4 Months by ICU**	**T1√**	**T2**	**T3**	**T4**	**T1√**	**T2**	**T3**	**T4**
**Variables to be controlled as possible confusion variables**	Old PUs identified upon entry to ICU (presents at the baseline). ▪ Other injuries such as burns, mask injuries, tube injuries, surgical wound dressings In ICU, PUs or dressing site (foam, hydrocolloid)				Total of patients with PUs up-to-baseline/150 patients by cluster (variable to be controlled) N(%)			
**1–4 Months by ICU**	**T1√**	**T2**	**T3**	**T4**	**T1√**	**T2**	**T3**	**T4**
**3-Characteristics of patients [demographic, Health status,**	Age (years), sex (M, F)				Mean (SD), N(%)			
	Body Mass Index (BMI)				Median (interquartile range) or mean (SD)			
	Patients´ Weight at admission				Median (interquartile range, IQR) or mean (SD)			
	Patients´ Height at admission				Median (interquartile range, IQR) or mean (SD)			
	Type of comorbidity to patient admission: Cardiovascular condition, Respiratory condition, Diabetes, Neurological, Malignancy of Carcinoma, Kidney Disease, Peripheral Vascular Disease, Cerebrovascular Accident, Transplant, dermatitis o eczema, documented malnutrition on admission, others.				N(%)			
	Length of hospital stay in ICU (Hours, days) (admission to ICU-Discharge from ICU)				Date: day/month/year Median (interquartile range, IQR) or mean (SD)			
	Patient-days involved in the study (by cluster and				Median (interquartile range, IQR) or mean (SD)			
**1–4 Months by ICU**	**T1√**	**T2√**	**T3√**	**T4√**	**T1√**	**T2√**	**T3√**	**T4√**
**4-Complications of patients in ICU**	Cardiovascular, neurological, sepsis, respiratory, delirium, TEP, musculoskeletal, shock, death				N(%)			
**4-Dates of the possible end of the following in ICU**	First ambulation in ICU Transference to hospital service Hospital transference Death				Day/Month/Year			
**1–4 Months by ICU**	**T1√**	**T2**	**T3**	**T4**	**T1√**	**T2**	**T3**	**T4**
**5-Characteristics of the cluster (or ICU)**	Type of hospital: Public, Private, University, other				N (%)			
	Skin Care Group Preventive care use-report on medical history				N (%)			

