The Hazard Ratio is an estimate that derives from the Cox model, and this is from the rate of risk index between the groups that received a higher frequency rate of postural changes than the groups that received conventional care of postural changes. An adjusted analysis by co-variables will be developed considering the related risk factors in the literature for developing PUs (age and comorbidity). The safety outcomes will be described as the registered events regarding posture shifts in each branch according to their frequency level in interventions A or B, and the association between posture shifts and their compilations will be explored. To detect early differences in the occurrence of events amongst the groups, we planned two interim analyses; once the 33 and 66% of the units are randomized, these internal analyses will be made using the sequential method [23].

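### The covariates named for the adjusted patient-level Cox analysis omit mechanical ventilation, the strongest risk factor in the protocol's own background

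*Protocol article*

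**What the plan says.** In the protocol article, the Statistical analysis section sets a primary analysis at ICU level (a ratio of incidence rates, no covariates stated) and a secondary analysis at patient level (a Cox model with a cluster-adjusted standard error). Straight after the Cox model it announces an adjusted analysis "considering the related risk factors in the literature for developing PUs (age and comorbidity").

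The Background section lists those risk factors: "mechanical ventilation (OR 23 [95% IC 6.42–86.6"]), "diabetes (OR 5.58 [95% IC 1.58–18.7"), "there is age (OR 2.14 [95% IC 1.27–3.62"]), and others.

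Table 1 (Data collection and procedure) defines comorbidity as conditions present on admission, beginning "Type of comorbidity to patient admission: Cardiovascular condition, Respiratory condition, Diabetes". A separate block, headed "Variables to be controlled as possible confusion variables", covers pre-existing ulcers, other injuries and dressings. Ventilation status at admission is in neither.

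Under Inclusion and exclusion criteria, eligible patients "are care-dependent for their complete mobilization (including unconsciousness, being under sedation or assisted ventilation"), and ICUs may be surgical, medical, neurological or mixed. Under Randomization and blinding, ICUs are allocated 1:1 in blocks with no stated stratification. The allocation is announced openly, and patient consent comes afterwards.

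**The concern.** The plan states a principle, adjustment for risk factors known from the literature, and then names a set that leaves out the largest factor on its own list. The article does not defer the choice of covariates to another document. It names them, and the names do not fit the Background.

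Ventilation is one route to care dependence, not a condition of entry, so ventilated and non-ventilated patients can both be enrolled. The ventilated share can be expected to differ between ICUs of different types. With 11 ICUs per arm, the arms can differ by chance. Because sites know their arm before patients enter, differential recruitment is also possible.

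At stake is the adjusted hazard ratio, which answers the protocol's second specific aim. It would be called adjusted while leaving any imbalance in this factor largely in place. Variation between ICUs that ventilation could explain would also stay in the standard error.

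**Working it through.** **1. The plan's own figure.** Inputs from Sample size: 0.075 vs 0.023, power 80%, ICC 0.035, 150 patients per ICU, 22 ICUs. The alpha is printed as 0.05% and taken here as 0.05, two-sided. Two proportions need 270 per arm. The design effect is 1 + 149 × 0.035 = 6.215, and 270 × 6.215 = 1,678 per arm. The plan has 22 × 150 / 2 = 1,650. The figure reproduces within 2% and does not depend on the covariates.

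**2. Ranking of the listed factors (Background).** Ventilation 23, diabetes 5.58, hemofiltration or dialysis 3.7, few position changes 3.63, age 2.14; vasoactive drugs, sedatives and low blood pressure lie between 1.02 and 1.09. So 23 / 5.58 = 4.1, and the lower limit for ventilation (6.42) exceeds every other point estimate.

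**3. Shift from an imbalance.** Assumptions: overall risk 0.075, a ventilated share π of 50%, 70% or 90%, and no treatment effect. Solve π·r1 + (1 − π)·r0 = 0.075 with [r1/(1 − r1)] / [r0/(1 − r0)] = OR. For OR 23 and π = 0.5, r0 = 0.0072 and r1 = 0.1428. A 10-point difference (45% vs 55%) gives

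(0.45 × 0.1428 + 0.55 × 0.0072) / (0.55 × 0.1428 + 0.45 × 0.0072) = 0.0682 / 0.0818 = 0.83.

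Risk ratio for a 10-point difference:

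| OR | π = 50% | π = 70% | π = 90% |
|---|---|---|---|
| 6.42 | 0.869 | 0.895 | 0.913 |
| 23 | 0.834 | 0.875 | 0.900 |
| 86.6 | 0.823 | 0.869 | 0.896 |

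The range is 0.82 to 0.91. The opposite imbalance gives the reciprocals, 1/0.913 = 1.10 to 1/0.823 = 1.22. At OR 23 and 70%, differences of 5 and 20 points give 0.94 and 0.77.

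**4. How likely a 10-point difference is by chance.** With 11 ICUs per arm, 150 patients each and 70% ventilated, SE = √{2 × [SD² + 0.7 × 0.3/150] / 11}. For SD 0.20 this is √(2 × 0.0414 / 11) = 0.087.

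| Between-ICU SD (points) | SE (points) | Chance of a difference above 10 points |
|---|---|---|
| 5 | 2.7 | about 0% |
| 10 | 4.6 | 3% |
| 15 | 6.6 | 13% |
| 20 | 8.7 | 25% |

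This treats all 22 ICUs as independent units. ICUs of one hospital share an allocation, so the true spread could be wider.

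**5. Variation between ICUs due to ventilation.** With SD 0.20, OR 23 and π = 0.5, the SD of ICU risk is 0.20 × (0.1428 − 0.0072) = 0.027. The implied ICC is 0.0271² / (0.075 × 0.925) = 0.011, against the planned 0.035.

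**The case against.** The case on the other side has several parts.

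- **Only a secondary analysis is touched.** A reader might infer that the primary result is left confounded. The documents do not support that: the covariate sentence belongs with the Cox model, and adding a term there changes nothing in the primary rate ratio. This stands.
- **Chance is not bias.** A reader might infer that an imbalance is present or likely. ICUs are randomized, so the expected difference is zero and may fall either way. No SD tried above makes a 10-point difference more likely than not. Chance variation between ICUs is already allowed for in the ICC and the cluster-adjusted standard error; step 5 gives under a third of the planned ICC. This stands. Differential recruitment after open allocation is possible, but enrolment is described as consecutive and nothing here quantifies it.
- **The adjustment may be wider than two covariates.** Table 1 names further variables to be controlled, so the set cannot be called strictly limited to age and comorbidity. But ventilation is not among those either.
- **The odds ratio may not transfer.** Its interval is very wide, its source population cannot be seen, and this trial takes only fully immobile patients, which may narrow the contrast. The model in step 3 implies a risk of 0.7% without ventilation, which sits poorly with the 3.3% to 52.9% the Background reports across ICUs. This weakens the magnitude, not the inconsistency.
- **Comorbidity may absorb part.** Respiratory and neurological conditions may correlate with ventilation, so the hazard ratio need not carry the whole imbalance.
- **The field may not be free.** The criteria give ventilation as an example of care dependence. They do not say that its status is recorded for each patient.

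None of this is a reason to omit the strongest listed factor.

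**Conclusion.** The point holds for the adjusted secondary Cox analysis. The named covariates do not follow the plan's own rule, and nothing in Table 1 fills the gap. The consequence is moderate: under assumed shares, a 10-point difference moves the risk ratio by roughly 9% to 18% downwards or 10% to 22% upwards, with a chance of about 0% to 25% over the SDs tried. This is well short of the planned ratio of 0.023/0.075 = 0.31. The ventilated share and its spread are assumptions, since the documents give neither. The figures are risk ratios that ignore person-time, so they indicate only the order of the shift in a hazard ratio. They do not show that the trial's main conclusion is at risk.

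**What to change.** Add mechanical ventilation status at ICU admission to the prespecified covariates of the adjusted Cox model, and add it to Table 1 as a yes/no baseline item so that it is recorded from the first patient. Use the enrolment value only: later ventilation may be affected by the intervention, and the protocol itself counts ventilation changes among the complications of repositioning. If it is left out on purpose, state the reason.

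The cost is one baseline field and one more model term. The primary rate ratio and the sample size stay as they are.
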